##### Secondary outcomes

Analysis of each element of the composite healthcare utilization metric will include separate logistic models for ICU care, unplanned hospitalization, additional unplanned procedure, ED visit, and unplanned clinic visit or testing endpoints. A Poisson model will be used to assess the number of ambulatory patient–provider interactions. The randomized cohort models will include the treatment group and stratification factor (stone location (kidney or ureter)) as independent variables. The observational cohort will include a treatment group and adjust for patient/surgical covariates (age, sex, body mass index (BMI), Charlson comorbidity index, stone location (kidney or ureter), and stone size) as independent variables. These analyses will be performed with the ITT population with a sensitivity analysis using the HCUmITT.

Additional HRQOL endpoints, including PROMIS® Pain Interference scores at 4–6 weeks change from preoperative scores, PROMIS® Pain Intensity *t*-score changes, and NIH LURN SI-10 urinary symptom score changes will be analyzed using ANOVA models as described for the pain interference primary endpoint analysis based upon cohort (RCT or observational). Similarly, ANOVA models will be used to assess ICIQ-S treatment satisfaction scores at postoperative days 7–10 and 4–6 weeks separately. These models will be similar to the primary analysis models based upon cohort for the pain interference primary endpoint except a preoperative score does not apply as satisfaction is only measured after the surgery. Alternatively, if the trajectory of change for the outcome is found to be linear, then a linear mixed model will be used to compare scores at 7 days and 4–6 weeks between treatment arms. The mixed models will add the independent variables of time and the interaction of arm and time, a random effect in the model for patient and an autoregressive covariance matrix. Each analysis will report means with 95% CI at each time for each group, with a model-based type-3 *F*-test comparing treatment groups.

Number of days off work will be described using medians with interquartile ranges by treatment arm in each cohort. Linear models like the treatment satisfaction score models will be used based upon cohort. If the assumptions of the linear model are violated, Poisson models will be used.

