## Introduction

### Background and rationale {6a}

In the USA, one in ten adults will have a kidney stone in their lifetime [1]. This chronic disease is recurrent and characterized by severe pain [2]. For patients unable to pass a stone, surgery is the mainstay of treatment [3]. With over 750,000 performed a year, ureteroscopy and lithotripsy are the most common procedure to remove or break up stones [4, 5]. At the end of ureteroscopy, a urologist may insert a temporary ureteral stent, a plastic flexible tube that allows urine to drain from the kidney to the bladder, which is later removed in the office, or at home by patient self-removal, which itself can provoke anxiety for patients [6, 7].

While the decision to place a ureteral stent is often made with good intentions, it is often unnecessary. Current US practice guidelines recommend stent omission if ureteroscopy is uncomplicated (e.g., no ureteral injury, stricture, or anatomic abnormality), which represents 80–90% of all cases. Despite this, stents are placed in up to 80% of all patients [8–10]. This utilization of stents comes at a cost to patients. Stents can have a detrimental effect on patient health-related quality of life (HRQOL), i.e., the impact that a disease has on mental, physical, and social well-being [11]. Stents result in flank pain, blood in the urine, and urinary symptoms in 80% of patients [12]. Data shows that 12.7–16.9% of patients visit the emergency department after ureteroscopy because of post-operative symptoms [8, 13–15], and 4–5.8% of these patients are hospitalized [16–19]. Total costs arising from stent-related problems while the stent is in place have been calculated to be a median $455 per patient (range $113–11,948) [20], making this among the costliest urologic disease to treat (expenditures in the US exceed $10 billion per year) [21]. Many patients develop stone recurrence during their lifetime, leading to multiple procedures and suffering.

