### Sample size {14}

The sample size was derived by the sample needed to power each co-primary endpoint for the RCT cohort. The larger sample size among the co-primary endpoints was used to estimate the final RCT cohort size. Each power calculation used a two-sided significance level of 2.5% to allow for two primary endpoints for a trial-level type I error of 5% as described below.

Postoperative days 7–10 PROMIS® Pain Interference change from pre-surgery is a co-primary endpoint; 101 participants per treatment arm will provide the RCT cohort with at least 90% power to detect a mean difference between stent placement vs. omission treatment groups of 5 points with an assumed standard deviation (SD) of 10 points, based on a two-sample *t* test (SAS 9.4), with a two-sided significance level of 2.5%. Previous work estimated that a clinically meaningful difference in PROMIS® Pain Interference is 2–6 points [25, 26]. A pilot study at our institution found an initial difference between stent omission and placement of 7.2 points with a SD of 13 for change and a SD of 10 at each time point. We expect our pilot may overestimate the treatment effect. Thus, we have targeted a difference of 5 points to represent a clinically significant target. A 10% loss to follow-up (failure to respond to the 7–10-day questionnaire) is assumed. Thus, 112 patients are needed per arm (total 224 patients). After consent, we estimate that 15% of patients who plan to be randomized will be unable to do so owing to intra-surgical factors that deem the procedure as complicated requiring 264 patients consented to the randomization cohort to attain 224 randomized patients.

Unplanned healthcare utilization within 30 days of ureteroscopy is the second co-primary endpoint.

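### Three secondary-outcome models need a different specification: Poisson for calls and messages, logistic regression for ICU care and hospitalization, and a two-visit mixed model with a redundant covariance term

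*Protocol article*

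**What the plan says.** All the models at issue are in the protocol article, section Secondary outcomes.

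- **Calls and messages.** "A Poisson model will be used to assess the number of ambulatory patient–provider interactions".
- **Binary components of healthcare utilization.** Each component, including ICU care and hospitalization, gets its own logistic model. The randomized cohort has two terms (treatment and stone location). The observational cohort has seven (treatment plus six patient and surgical covariates).
- **Secondary questionnaire scores.** The main plan is an ANOVA-type model like the one for the pain co-primary. The alternative, used if the trajectory turns out to be linear, is a mixed model comparing 7 days with 4–6 weeks. It has time, arm by time, and "a random effect in the model for patient and an autoregressive covariance matrix".
- **Days off work.** Linear models come first. "If the assumptions of the linear model are violated, Poisson models will be used".

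The only event rates are background figures in Background and rationale {6a}: an emergency department (ED) visit rate of 12.7–16.9%, and then "4–5.8% of these patients are hospitalized". No ICU rate is given, and no mean or variance for calls and messages.

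**The concern.** One symptom can lead to several calls or messages from the same patient, so the variance of the count may well exceed its mean. Model-based Poisson errors assume the two are equal.

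ICU care, and possibly hospitalization, may produce so few events that an arm is empty and the maximum-likelihood odds ratio is infinite. The stone-location-by-treatment interaction, which the additional-analyses section {20b} also plans for secondary endpoints, would spread the same events over four cells.

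A random patient effect and an autoregressive residual both describe within-patient correlation, and two visits cannot separate them. A linearity condition on two points cannot fail, so it does not choose between the ANOVA models and the mixed model.

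At stake are the intervals and p-values of secondary outcomes, and whether some of these models can be fitted as written.

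**Working it through.** **Denominators.** The article states no power, event count or dispersion for secondary outcomes, so the figure to reproduce is the sample size in Sample size {14}: "101 participants per treatment arm will provide the RCT cohort with at least 90% power" for a difference of "5 points with an assumed standard deviation (SD) of 10 points", at a two-sided 2.5% level. The noncentral t distribution gives power 0.898 at 100 per arm and 0.901 at 101, so 101 reproduces. Dividing by 0.90 gives 112.2, against the stated 112 per arm (224 in total). The observational cohort is 449 (314 stented, 135 not).

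**1. Calls and messages.** Let φ be variance divided by mean. The true standard error is √φ times the model-based one, so the actual level of a nominal 5% test is 2(1 − Φ(1.96/√φ)). The simulation used negative binomial counts, 112 per arm, means 0.5 to 3 and 10,000 runs per setting. All values of φ are assumptions.

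| φ | √φ | Level, formula | Level, simulated, model-based errors | Level, simulated, robust variance |
|---|---|---|---|---|
| 1 | 1.00 | 5.0% | 4.7–4.9% | 4.9–5.0% |
| 1.5 | 1.22 | 11.0% | 10.7–11.0% | 5.0–5.6% |
| 2 | 1.41 | 16.6% | 15.9–16.6% | 5.1–5.5% |
| 3 | 1.73 | 25.8% | 24.7–26.0% | 5.3–6.0% |
| 4 | 2.00 | 32.7% | 31.6–33.7% | 5.3–6.0% |

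**2. Rare components.** Expected events are N × rate. With the same rate p in both arms, the chance that at least one randomized arm is empty is 1 − [1 − (1 − p)^112]².

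- *ED visits:* 224 × 0.127 = 28.4 to 224 × 0.169 = 37.9 randomized; 449 × 0.127 = 57.0 to 449 × 0.169 = 75.9 observational. These are not sparse.
- *Hospitalization, if 4–5.8% is of all patients:* 224 × 0.04 = 9.0 to 224 × 0.058 = 13.0 randomized events, with a 2% to 0.2% chance of an empty arm. Observational: 18.0 to 26.0 events, and division by seven terms gives 2.6 to 3.7 events per term.
- *Hospitalization, if 4–5.8% is of ED visitors:* 224 × 0.127 × 0.04 = 1.1 to 224 × 0.169 × 0.058 = 2.2 randomized events, with an 81% to 55% chance of an empty arm. Observational: 2.3 to 4.4 events, or 0.3 to 0.6 per term.
- *ICU care, assumed rate 0.1% to 1%:* at 0.1%, 0.999^112 = 0.894 and 1 − 0.106² = 0.989. At 1%, 0.99^112 = 0.324 and 1 − 0.676² = 0.54. The chance of an empty arm is therefore 54% to 99%.

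**3. Mixed model.** With patient variance τ², residual variance σ² and autocorrelation ρ, two visits give Var = τ² + σ² and Cov = τ² + ρσ²: three unknowns, two moments. A REML fit to simulated two-visit data shows this:

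| ρ fixed at | τ² | σ² | REML log-likelihood | Arm effects | SE |
|---|---|---|---|---|---|
| 0 | 65.38 | 33.56 | −1187.7327 | 1.389, 1.287 | 1.3292 |
| 0.3 | 51.00 | 47.95 | −1187.7327 | 1.389, 1.287 | 1.3292 |
| 0.6 | 15.03 | 83.91 | −1187.7327 | 1.389, 1.287 | 1.3292 |

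The likelihood is flat in ρ, and only the split of the variance moves. The effects and standard errors do not change. With a third visit as a response the likelihood does vary (−1730.61 at ρ = 0, −1728.15 at 0.2, −1732.98 at 0.6), so ρ can then be estimated.

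**The case against.** Much of the case on the other side stands.

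- A reader might infer that the mixed model leaves secondary outcomes without valid error bars. It does not: the contrasts and their standard errors are the same at every ρ. The model is also only an alternative to the ANOVA models.
- Two responses are certain only for ICIQ-S, which is measured only after surgery. The other scores also have a preoperative value. If that enters as a response, the covariance is identified and linearity can be checked. The article does not say whether it does.
- A reader might take the 11–34% error rates as the trial's own. They rest on an assumed dispersion. Naming a Poisson model does not exclude a robust or scaled variance, and that detail may be in an analysis plan that is not shown.
- A reader might infer that all the logistic models are starved of events. ED visits are not, and no figure supports it for additional procedures or clinic visits and testing. On the all-patients reading, the two-term randomized model for hospitalization is usable.
- A reader might extend the problem to the co-primary. The randomized win ratio has a bootstrap interval and does not use the Poisson model. Nothing shows that calls and messages decide many of its pairs.

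The objection does not remove the point. The section names model families, a covariance structure and a trigger, and unlike the primary-outcome sections it does not refer the reader to the analysis plan for details.

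**Conclusion.** The point holds for secondary outcomes only, as a change that should be made rather than one on which the trial depends.

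1. **Calls and messages.** Intervals are too narrow by √φ if the counts are overdispersed and the errors are model-based. Overdispersion is plausible but not documented.
2. **Rare components.** Ordinary logistic regression is unsuitable for ICU care over the assumed range of rates. It is fragile for hospitalization, with at most 2.6–3.7 events per term in the observational model on either reading of the background rate.
3. **Mixed model.** It is over-parameterised wherever only two postoperative responses enter, and there its trigger cannot discriminate. The harm is possible non-convergence and a choice of analysis left open or made after seeing the data.

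The Poisson fallback for days off work is a minor addition. The outcome covers the first 7 days and so cannot exceed 7, whereas a Poisson count has no ceiling. No size can be put on this from the document.

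**What to change.** - **Calls and messages:** specify Poisson regression with a robust variance, or a negative binomial model. The cost is wider intervals if the counts are overdispersed.
- **Hospitalization:** use Firth-penalised or exact logistic methods.
- **ICU care:** report counts by arm descriptively, without a model.
- **ED visits:** no change.
- **Mixed model:** drop either the random patient effect or the autoregressive term, or use categorical visit with an unstructured covariance. Remove the linearity condition and state in advance which of the ANOVA and mixed models is used for each score.
- **Days off work (optional):** name an ordinal or bounded-count model as the fallback.

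These are wording changes to the protocol or analysis plan, best made before database lock. They need standard software, no new data and no change to the sample size.

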### Interim analyses {21b}

An interim analysis after 396 patients are accrued is planned for confirmation of assumptions and re-estimation of sample size and power. Measures to be assessed include the proportion of patients who agree to join the randomization trial arm, the overall standard deviation of the primary endpoint, pain interference at days 7–10 change from pre-surgery, the proportion stented in the observational arm, and the intraclass correlation (ICC) in the observational arm. The sample size and power of each trial cohort will be reassessed based upon the interim analysis estimates compared to the assumed estimates. The results will be shared with the trial team and discussed with the funder.

### Methods for additional analyses (e.g., subgroup analyses) {20b}

Planned sub-group analyses will include an analysis by stone location for the primary and secondary endpoints. The methods will be similar to the analysis plan for each endpoint. A fixed effect for the statistical interaction of stone location and treatment arm will be used in the statistical models to measure a signal for a difference in outcome by stone location. A separate analysis for each stone location will be performed for the health care utilization Win Ratio outcome using analysis methods described for each cohort in the primary analysis plan.

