With a modest probability of improvement in the reduction of healthcare utilization in ureteroscopy with stent omission, the impact in morbidity reduction and cost reduction would be great. There are no current estimates in the literature that help inform a minimum important difference for the win ratio estimate of healthcare utilization, our co-primary endpoint. So, we reasoned that a marginal probabilistic index, which is the effect size measure corresponding to the nonparametric Mann–Whitney *U* statistic that is used to test the hierarchical composite “win ratio” endpoint [27], of at least 67%, would be impactful as the study could conclude that a randomly chosen participant with stent omission has a two-thirds or greater probability of lower healthcare utilization than a randomly chosen participant treated with a stent. In the RCT with a two-sided 2.5% alpha and requiring 90% power to detect a treatment effect of 67%, 72 patients would be required per treatment arm. The sample size is based on the Finkelstein and Schoenfeld methods [28] for analysis of hierarchical composite endpoints, later called the win ratio by Pocock et al. based on the nonparametric Mann–Whitney *U* statistic [29]; the formula is provided in Yosef et al. [30].

The observational cohort sample size was derived from an assumption that 1/3 of patients approached and consented would be willing to be randomized. Thus, the observational cohort will consist of the estimated 2/3 (528) of patients who are approached and decline the RCT. With those assumptions, we find the following power for each primary endpoint.

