## Assignment of interventions: allocation

### Sequence generation {16a}

Participants in the randomization cohort will be randomized intraoperatively using an online computer-based system (https://randomize.net/) to either stent omission or stent placement in a 1:1 ratio. This will take place after the completion of the lithotripsy portion of the procedure and verification of second-stage eligibility by the operating urologist. Blocked, stratified randomization based upon surgeon-classified stone location (renal only versus ureteral with or without renal), with random block sizes will be used to ensure group balance.

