#### Randomized cohort analysis

The analysis of the hierarchical composite endpoint of healthcare utilization using the Win Ratio [29] in the RCT will use the ITT population and will use the unmatched approach [35, 36]. The composite healthcare utilization metric within 30 days will be an assigned score for each patient based upon the highest ureteroscopy-related utilization level that they participate in with levels defined in decreasing order: (6) Hospitalization and ICU care; (5) unplanned hospitalization; (4) unplanned additional operating room or interventional radiology procedure; (3) emergency department (ED) visit; (2) ambulatory encounter: clinic visit; and (1) number of ambulatory patient/provider interactions. Then the rank of each patient in the stent omission arm will be compared to each patient in the stent arm using the unplanned healthcare utilization ranking rules described above such that each pair will have a winner. Summary statistics for the hierarchical composite win ratio endpoint will be presented, including the number of total pairs, and number and proportion of pairs that favor stent omission for each component of the unplanned healthcare utilization outcome. The number of winners and losers for stent omission and corresponding win ratio will be reported with the 97.5% (bootstrapped-based) confidence interval and *p*-value based on the Chi-square statistic. In addition, the probability of a participant with stent omission doing better than a participant with a stent will be presented. It is not expected to have missing data for this endpoint but if there is then multiple imputation will be used. Sensitivity analysis will be conducted with the same analysis in the healthcare utilization modified intent-to-treat (HCUmITT, see Sect. 20c) population to assess the robustness of the effect found in the primary analysis.

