#### Observational cohort analysis

The same general approach used in the RCT will be applied to the observational study with the healthcare utilization rank for each patient and the rules for comparing pairs of patients between arms. However, to address possible clustering among surgeons and sites while protecting unbiasedness of treatment effects and to preserve power, the analysis approach of Dong et al. [36] will be implemented. Specifically, this approach incorporates the notion of risk-matching by forming strata according to risk groups (as described by Pocock et al. [29]) without resulting in loss of information by losing matched pairs when there is an imbalance in sample size between groups. The stratified approach uses the unmatched method to calculate the win ratio statistics within stratum, thus providing an intermediate position between the matched pairs approach and the unmatched approach. Specifically, we will include site in the determination of risk strata. To form risk group strata, the outcome of healthcare utilization categorized as yes versus no will be modeled using a logistic model with fixed effects including baseline variables: site, stone location (kidney only vs ureter), stone size, and Charlson comorbidity score. A risk score for each patient will be obtained using the logistic model’s coefficients. Stratification will be performed based upon risk score. Risk score groups will be defined using natural bins (if they are apparent) or percentiles. Then, within each stratum, an unmatched approach will be used to calculate the win ratio. The overall win ratio will be estimated using the Mantel–Haenszel-type weight and reported with a 97.5% confidence interval. The method for adjustment will be described in detail in the SAP and finalized prior to data lock. Sensitivity analysis will be conducted with the same analysis in the HCUmITT population to assess the robustness of the effect found in the primary analysis.

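### The stone-location subgroup analysis of the co-primary utilization win ratio names no comparison between locations, so it gives no valid basis for a statement that the effect differs

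*Protocol article*

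**What the plan says.** The relevant text is in the protocol article under Methods for additional analyses {20b}. It sets the scope: "Planned sub-group analyses will include an analysis by stone location for the primary and secondary endpoints". For endpoints analysed by regression it gives a method that addresses effect modification: "A fixed effect for the statistical interaction of stone location and treatment arm will be used in the statistical models to measure a signal". The stated aim is an indication of whether the outcome differs with stone location. For the utilization composite, which Outcomes {12} lists as co-primary, it then states: "A separate analysis for each stone location will be performed for the health care utilization Win Ratio outcome", using each cohort's primary method.

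Those primary methods are set out under Statistical methods {20a}:
- In the randomized cohort, the win ratio analysis "will use the ITT population and will use the unmatched approach". It reports a bootstrap 97.5% interval and a chi-square p-value.
- In the observational cohort, win ratios are computed within risk-score strata and pooled: "The overall win ratio will be estimated using the Mantel–Haenszel-type weight and reported with a 97.5% confidence interval". Stone location is one of the predictors in the risk model.

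Sequence generation {16a} defines two location levels: renal only, and ureteral with or without renal stones. Location is also the randomization stratification factor.

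**The concern.** The interaction sentence can act only where there is a model to hold the term. An unmatched win ratio, or a stratified one pooled with Mantel–Haenszel-type weights, has no such coefficient. For this endpoint the plan therefore produces two win ratios, each with its own interval and, in the randomized cohort, its own p-value, and nothing that compares them.

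Two separate tests do not test a difference. When the true effect is the same in both locations, one result can cross the threshold and the other miss it by chance or because one location has fewer patients. Stone location is the one subgroup factor the section names, and it bears on who might go without a stent. A pair of results that disagree on significance could easily be read as saying that omission reduces utilization for one kind of stone only.

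**Working it through.** **Inputs from the protocol (Sample size {14}; Sequence generation {16a}):** two-sided alpha 2.5%, power 90%, target marginal probabilistic index 67%, 72 per arm stated for the win ratio, 112 per arm (224 in total) to be randomized, 1:1 allocation. **Assumed:** the split by stone location, taken as 50:50 to 30:70; no ties, in keeping with the protocol's statement that every pair has a winner.

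**Step 1: reproduce the plan's figure.** The Mann–Whitney sample size formula with equal arms is N = (z₁ + z₂)² / [12 × 0.25 × (p − 0.5)²], with z₁ = 2.241 and z₂ = 1.282.
- N = 12.41 / (3 × 0.17²) = 12.41 / 0.0867 = 143.15, or 72 per arm, as stated.
- The same formula gives detectable indices of 60.1% at 202 per arm and 64.3% at 101 per arm, also as stated.

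**Step 2: power within one location.** With N patients in a location, SE = 1/√(3N) and power ≈ Φ[(p − 0.5)/SE − 2.241].
- Even split, N = 112, SE = 0.0546. At 67%: Φ(3.116 − 2.241) = 80.9%. At 60%: Φ(1.833 − 2.241) = 34.2%.
- 30:70 split, N = 67.2 and 156.8, SE = 0.0704 and 0.0461. At 67%: 56.8% and 92.6%. At 60%: 20.6% and 47.1%.

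**Step 3: chance that exactly one location is significant when the effect is identical in both.** The locations share no patients, so the chance is A(1 − B) + B(1 − A), where A and B are the two powers.

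| Common true index | 50:50 | 40:60 | 30:70 |
|---|---|---|---|
| 50% (no effect) | 4.9% | 4.9% | 4.9% |
| 60% | 45.0% | 45.8% | 48.3% |
| 67% | 30.9% | 34.3% | 44.2% |

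For example, 67% with an even split: 2 × 0.809 × 0.191 = 0.309. If each location were read at two-sided 5%, the 67% row would run from 21.7% (50:50) to 34.0% (30:70), and the 60% row from 49.5% to 53.4%.

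**Step 4: check by simulation, and effect of a direct contrast.** In 4,000 simulated trials per scenario, discordance was 27% (50:50) to 40% (30:70) at 67%, 47% to 50% at 60%, and 5% to 6% with no effect. A z test of the difference between the two win probabilities at two-sided 5% gave a false signal in 4.6% to 5.8% of trials across the same scenarios, close to nominal.

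**Step 5: power of that contrast.** With an even split, SE of the difference = √(2/336) = 0.0772.
- 67% against 50%: Φ(0.17/0.0772 − 1.96) = Φ(0.24), about 60%.
- A 10-point gap: Φ(0.10/0.0772 − 1.96) = Φ(−0.66), about 25%.

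**Observational cohort.** The same formula at 202 per arm, ignoring risk strata and clustering, gives discordance of 48.5% (even split) to 56.5% (30:70) at an index of 60%, and 5.1% to 16.1% at 67%.

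**The case against.** The strongest reply is that the protocol commits no inferential error. It says separate analyses will be done; it does not say that a difference will be declared when one is significant and the other is not. A reader might infer that rule, but the text does not contain it, so the discordance rates above are not false-claim rates. They show what the separate results would look like, and they become error rates only if someone reads them that way. This part of the reply stands.

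Three other stronger readings also go too far:
- That each location is underpowered. At the planned index of 67% with an even split, each has about 81% power. The shortfall appears with unequal splits or smaller effects.
- That effect modification on utilization goes untested. Each component of the composite is a secondary endpoint with its own logistic or Poisson model, and the interaction term applies there. The composite itself is what lacks a test.
- That the trial's main conclusion is at risk. It is not.

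It can also be said that a heterogeneity statistic is a detail for the statistical analysis plan. That is less persuasive. The section does not leave the method open: it fixes an interaction for modelled endpoints and separate analyses for the win ratio, and unlike the passages on risk adjustment and imputation it defers nothing. Fixing separate analyses does not forbid a contrast, but an analysis plan that simply follows this text would not contain one.

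**Conclusion.** The point holds in this limited form. For the co-primary win ratio, the method fixed in {20b} cannot answer the section's own question of whether the effect differs by stone location. With a common true effect in the randomized cohort, results that disagree on significance would be frequent: about 31% to 44% of trials at an index of 67% and 45% to 48% at 60%. With no effect the rate is about 5%, and it can also be low in the observational cohort if the index is 67%. These figures rest on an assumed location split, the no-ties variance behind the protocol's own sample size, and each location being tested at two-sided 2.5%. The consequence is confined to subgroup statements; the co-primary test, its error rate and the sample size do not change.

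**What to change.** Keep the two location-specific win ratios and add one contrast between them in {20b}:
- **Randomized cohort.** Estimate the difference in ln win ratio, or in win probability, between renal-only and ureteral stones. Give it a bootstrap interval, in line with the primary analysis, by resampling within location and arm. A z test, dividing the difference by √(SE₁² + SE₂²), would also serve, but the plan specifies a bootstrap interval and not a standard error of ln win ratio, so the standard errors would have to be obtained.
- **Observational cohort.** Form the risk strata separately within each location. Stone location is constant there and drops out of the risk model. Pool within location as planned, then take the same contrast.
- **Reporting.** Show both win ratios with the contrast, its interval and p-value. Base any statement about a difference by location on the contrast alone.

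The cost is modest: a few lines of analysis in the randomized cohort and a refitted risk model per location in the observational one. The contrast has low power, as step 5 shows, so the text should add that a non-significant result is not evidence that the effect is the same in both locations.
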